## Abstract

**Background:**

About 4 % of children in Hong Kong have attention deficit hyperactivity disorder (ADHD). The parents of children with ADHD report higher levels of stress and show more negative parenting behavior. Medication and behavior training are evidence-based treatments, but both show significant limitations. In short, medical treatment is not suitable for preschool children and would suppress growth, whereas parents under stress may not be capable of consistently applying behavior management skills. Mindfulness training can improve attention and facilitate cognitive development and overall functioning. It has been widely adopted as a treatment option in health care, but its application in a family context is limited. In this context, a family-based mindfulness intervention (FBMI) has been developed to promote the attention and mental health of children with attention symptoms and to reduce the stress experienced by their parents. This article describes the design and conduct of the trial.

**Methods/design:**

A multicenter, 8-week, waitlist, randomized controlled trial of FBMI is currently being conducted in Hong Kong (from mid-2015 to mid-2016). Its effectiveness will be examined by comparing the participants who receive treatment to those in a waitlist control group. The study population consists of one hundred twenty children with ADHD, or with symptoms of inattention and hyperactivity, between 5 and 7 years of age and their parents. To be included in the study, the children are required to meet or exceed the borderline cutoff score of the Chinese version of the Strengths and Weaknesses of ADHD Symptoms and Normal Behaviors Rating Scale (SWAN-C). The primary outcome measures are the children’s ADHD symptoms and behavior and the parents’ stress. The secondary outcome measures include the children’s overall behavioral problems and performance on the Attention Network Test, the parents’ ADHD symptoms, the parents’ mindful parenting scores, and heart rate variability of parents.

**Discussion:**

This study is probably the first randomized controlled trial of FBMI for young children and their caregivers. A rigorous design and multiple outcome measures are used to examine the effectiveness of FBMI. If the hypotheses are confirmed, FBMI may serve as an additional treatment option for children with ADHD.

**Trial registration:**

This study is registered with the Chinese Clinical Trial Registry (reference number: ChiCTR-IOR-15007292). Registered 28 October 2015.

## Background

Attention-deficit hyperactivity disorder (ADHD) is a childhood psychiatric disorder that is characterized by the core symptoms of inattention, hyperactivity, and impulsivity with an early onset [1]. The prevalence of ADHD is between 1.5 % and 8 %, depending on the diagnostic criteria used [2]. A study in Hong Kong estimated that 3.9 % of adolescents had received a diagnosis of ADHD [3]. More children in the community have reported problems of inattention, and studies have found an association between children with subclinical attention problems and problems with peer relationships and negative parenting [4].

Most children with ADHD have significant impairment of their executive functions (EFs). They show consistently worse performance on EF tasks than their typically developing counterparts [5]. EFs are a set of fundamental mental processes associated with the use of higher cognitive abilities that contribute to overall neuropsychological functioning [6]. The core EFs are cognitive flexibility, inhibition (self-control, self-regulation), working memory, problem-solving, reasoning, and planning [7]. When children exhibit EF deficits, they have greater difficulty moderating their behavior and show problems in working memory recall; self-regulation of mood, motivation, and arousal; internalization of verbal communication; and reconstitution of language and motor behavior [8]. Therefore, EFs are more important than intelligence quotient for school readiness [9]. Children with less self-control (less persistence, more impulsivity, and poorer attention regulation) between 3 and 11 years of age tend to have worse health, earn less, and commit more crimes 30 years later than those with better self-control as children, after controlling for intelligence quotient, gender, social class, and other factors [10].

ADHD is also associated with disturbances in the family and poorer parenting practices [11, 12]. The parents of children with ADHD report less marital satisfaction and more conflict than those of children without ADHD [13]. Challenging child behavior evokes harsh parenting, which is defined by intense hostility and negative emotionality and is hypothesized to influence the development of oppositional and conduct problems via a process of mutual reinforcement [14]. The parents of children with ADHD report higher levels of stress, lower levels of social support and quality of life, and less parenting satisfaction than parents of children without ADHD [15]. In view of the reciprocal and dynamic interactions between children with ADHD and their parents, the treatment of ADHD should consider the promotion of calm and consistent discipline and emotional responsiveness in parenting [16].

Currently, evidence-based treatment for ADHD focuses predominately on the use of medication and behavior therapy, but both options have limitations. Although the use of stimulant medications is generally considered to be evidence-based practice [17], the sustained use of stimulants over time is associated with growth suppression and may induce deleterious side effects that are untenable for many individuals, and thus it should not be preferable for young children [18, 19]. The parents of children with ADHD may learn parenting skills from behavior therapy; however, when they are under stress or have their own psychopathology, they may not be able to properly carry out parenting skills, and may feel frustrated and negatively reinforce parent–child conflicts [20]. A family-based intervention would be advantageous because both children and their parents could benefit from improvement of attention and emotional management.

### Mindfulness and its potential application in children and in a familial context

Mindfulness training has been shown to be an effective tool with which to enhance the self-regulation of attention in individuals with ADHD, in conjunction with other evidence-based treatments [21, 22]. Mindfulness training is expected to improve attention in three aspects: orienting attention, alerting attention, and executive attention [23, 24]. Orienting attention concerns the use of all available sensory inputs in the perceptual field to direct and select situation-appropriate information. Alerting attention refers to sustaining attention by achieving and maintaining a vigilant state. Executive attention involves examining, monitoring, and resolving conflicts among one’s ongoing behavioral reactions to the immediate environment [25]. Mindfulness training may improve the ability to strengthen attentional processes [22, 26]; it not only promotes the EFs of children with ADHD, but also improves parents’ self-regulation in response to their child’s challenging behavior and alters the dysfunctional patterns in their parenting behavior [27].

Evidence of mindfulness-based intervention is emerging, specifically for families with children with ADHD. A randomized controlled trial of mindfulness-based cognitive therapy was conducted in 25 children between 9 and 13 years of age who had a mixture of attention problems and ADHD diagnoses [28]. The children showed significantly fewer attention-related problems after the intervention. A mindfulness-based curriculum developed for 409 children from kindergarten to sixth grade from low-income families and ethnic minorities [29] resulted in improvements in classroom behavior, including attention, self-control, and caring for others. However, no control group was used, and the effects on the children’s other developmental aspects remain unclear. The results of an 8-week mindfulness training course conducted in 22 children between 8 and 12 years of age with ADHD and their parents indicated significant reductions in the children’s ADHD symptoms and in their parents’ inattention and hyperactivity symptoms [30]. In a study of the same program in 10 adolescents aged 11 to 15 with ADHD and their parents, the adolescents, parents, and tutors all reported improvements in attention and behavioral problems [31]. Overall, the results are positive but three of four studies were based on small samples, and except the first study, only a simple pretest-posttest comparison design was adopted for outcome evaluation.

There is increasing evidence for the application of mindfulness-based interventions in Chinese populations [32, 33]. However, this project is one of the earliest attempts to apply mindfulness training in children and families, and to the best of our knowledge, no studies of mindfulness training in parents and young children have been published. With reference to the above overseas studies, mindfulness-based interventions for children with ADHD and their parents may be acceptable and feasible, but the published studies have numerous methodological limitations, including small or heterogeneous samples and uncontrolled or nonrandomized designs. Some studies did not involve parents, and most studies involved children above 8 years old, but not young children.

### Study objectives

The objectives of the project are (1) to reduce the symptoms of inattention and hyperactivity of children with ADHD; (2) to reduce the stress of parents; and (3) to examine the effectiveness of family-based mindfulness intervention (FBMI) in Chinese families of children with ADHD or with symptoms of inattention and hyperactivity. The following hypotheses are proposed.We expect FBMI to reduce the symptoms of inattention and hyperactivity of children relative to those in a wait-list control group.We expect FBMI to reduce the internalizing and externalizing symptoms of children relative to those in a wait-list control group.We expect FBMI to reduce parental stress, achieve better well-being, as reflected in heart rate variability (HRV) parameters, and improve parent mindfulness relative to those in a wait-list control group.

## Methods/design

### Study design overview

The families of children with diagnoses of ADHD or with symptoms of inattention and hyperactivity are being recruited to participate in this study. The rationale for not restricting the study to children with formal diagnoses was that many children are first assessed by professionals after 6 in Hong Kong, and therefore many children with severe inattention and hyperactivity symptoms have not yet received a diagnosis.

A flowchart of the recruitment and implementation of this waitlist randomized controlled trial is illustrated in Fig. 1. All eligible families are randomized into a treatment group or a wait-list control group. The FBMI is delivered in a group format. All families in the waitlist control groups will undergo the same program after the posttest of the treatment groups. Three local non-government organizations in Hong Kong are participating in the study. The programs are conducted in the three collaborators’ district family service centers.

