**Fig. 1 Fig1:**
[figure not shown]
Flow diagram of participant allocation

The parent program of the FBMI was designed by the Principal Investigator by means of some adaptations to two overseas mindful parenting programs [34, 35]. The program lasts for 6 weeks, and each session lasts 1.5 h. Each parent program can accommodate 15 to 20 parents. A protocol was prepared by the first author, and the session themes and key contents are summarized in Table 1. The parent programs are implemented by instructors employed by the research team or social workers from the three NGOs who have completed training organized by the Principal Investigator. All parent group instructors completed an 8-week mindfulness-based stress reduction program or mindfulness-based cognitive therapy program. Additional training was provided by [name], the trainer of another mindful parenting program [35], or the first author.

**Table 1 Tab1:** Child program of Family-based Mindfulness Intervention (developed by Snel, 2014)

Session	Theme	Goal
1	A for attention	- Establish motivation of be attentive and mindful
		- Use breathing as a beginning of exploration of attention
2	Exploring our body	- Introduce mindful movement exercises
		- Expand awareness of body sensation
3	Tasting, Smelling, Hearing, Seeing and Feeling	- Introduce the use of multiple senses in understanding our inner and outside world
4	Feel our feelings	- Learn to be aware and to describe feelings
5	Accepting feelings	- Acknowledge feelings of self and others
		- Experience the importance of accepting feelings
6	Conscious movement	- Bring attention and awareness to self and others
7	The power of awareness and thoughts	- Experience the application of mindful attention and thoughts in daily life
8	Being nice is good	- Consolidate learning
		- Practice of lovingkindness

For the child program, FBMI follows the child mindfulness program “Mindfulness Matters” (the green book for children 5 to 8 years of age) [36]. The program includes four to six children, and each session lasts 1 h. All group instructors possess a professional degree in social work, education, or clinical psychology and have been certified as instructors by completing the 6-day “Mindfulness Matters” professional training program.

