During the fourth and sixth sessions of the parent program, 30-min joint activities are included. This design helps the family members to practice mindfulness together and to review their learning and progress in each other’s presence. The session themes of the child program are shown in Table 2. Participants in the wait-list group will receive the same intervention after the families from intervention group complete FBMI. The research team estimated that the study would be conducted in five cycles, with each cycle consisting of 24 families randomized into an intervention group and a waitlist control group.

**Table 2 Tab2:** Mindfulness training for parents (developed by the [name])

Session	Theme	Goal
1	Stress of being a parent	- Establish motivation to learn mindfulness for promotion of family health
		- Introduce mindfulness training
		- Introduce body scan
2	Automatic reactions	- Introduce stretching
		- Notice physiological, emotional and cognitive reaction in stressful moments of parenting
		- Use of mindful breathing and nonjudgmental attitude in managing the reaction in parenting
3	Respond to children mindfully	- introduce mindfulness to breath and body
		- Further notice reactive patterns in parenting
		- Introduce three minute breathing as coping
		- Practice deep listening in mindfulness
4	Quality parenting	- Joint session: practice with children, progress review
		- Introduce mindfulness to sounds and thoughts
		- mindful living for ADHD children and family caregivers
5	Facing difficulties with kindness	- Exploring difficulties with mindfulness practice
		- Introduce lovingkindness practice for self-care, and care of others
6	Self-care of parents	- Joint session: practice with children, progress review
		- Care plan of children and self
		- Consolidate learning

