### Statistical analysis

The baseline characteristics of the intervention group and the waitlist control group will be compared by analysis of covariance for continuous variables and chi-square tests for categorical variables. The baseline factors include the age of the children and the parents, the sex of the children and the parents, the children’s medication status, and the SWAN scores. The effects of FBMI will be tested by analysis of covariance, comparing the FBMI group (arm 1) to the wait-list control group (arm 2). All analyses will be carried out according to the intention-to-treat approach. The participants’ missing values will be imputed using the last-observation-carried-forward method. A two-sided *P* value of 0.05 or less will be considered be statistically significant.

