### Estimation of sample size

Because no studies of FBMI have been performed in the families of young children with ADHD, and because the effect sizes of studies of psychosocial treatments vary, the research team adopted an estimated effect size of 0.6 for changes in child attention and behavior. Based on a one-sided type I error of 5 % and 80 % power to detect statistically significant differences between the FBMI and wait-list control groups, the required sample size per arm is 45. Considering an attrition rate of 15 %, more than one hundred six families should be recruited for the study.

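### The intervention is delivered in groups, but the ANCOVA and the 45 per arm treat treated families as independent: type I error rises with any positive within-group correlation, and 80% power at that size is not assured

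*Protocol article*

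**What the plan says.** All references are to the protocol article.

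- **Delivery.** Study design overview: "The FBMI is delivered in a group format". On the child side, "The program includes four to six children, and each session lasts 1 h". A parent group has a stated capacity of 15 to 20. Recruitment is planned in "five cycles, with each cycle consisting of 24 families randomized into an intervention group and a waitlist control group". Wait-list families receive the program only after the treated groups' posttest.
- **Randomization.** Study sample: families are allocated one by one, not as groups.
- **Analysis.** Statistical analysis: "The effects of FBMI will be tested by analysis of covariance, comparing the FBMI group (arm 1) to the wait-list control group", by intention to treat with last observation carried forward, at "A two-sided *P* value of 0.05 or less". Delivery group and instructor are not mentioned.
- **Sample size.** Estimation of sample size: an "estimated effect size of 0.6 for changes in child attention and behavior", then "Based on a one-sided type I error of 5 % and 80 % power", and from these "the required sample size per arm is 45". The only inflation is for 15% attrition, giving just over 106 families. The plan recruits 120.

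**The concern.** Treated children share a group and an instructor with three to five others, and treated parents share a larger group. Outcomes in the same group may move together because of the instructor, the group climate or the joint parent–child activities. Wait-list families share nothing comparable before the posttest. This is a partially nested design: individual randomization, with clustering in one arm only.

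An ordinary ANCOVA counts each treated family as a full independent observation. If the within-group correlation is positive, the treated-arm mean varies more than the model assumes. The standard error is then too small, the confidence interval too narrow and the P value too low. The same assumption in the sample size makes the stated power optimistic. Child symptoms and behavior and parent stress are all primary outcomes, so this bears on the trial's main inference.

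**Working it through.** **1. Reproduce the plan's figure.** Inputs from Estimation of sample size: d = 0.6, power 80%. With n = 2(z₁ + z₂)²/d²:
- two-sided 5%: 2 × (1.960 + 0.842)²/0.36 = 43.6, so 44; with the t distribution 44.6, so **45**;
- one-sided 5%: 2 × (1.645 + 0.842)²/0.36 = 34.3, so 35; with the t distribution 35.04, so 36.

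Attrition: 90/0.85 = 105.9, so 106. The stated 45 is therefore a two-sided figure for independent observations, with a design effect of exactly 1. The one-sided wording does not give 45. That conflict is a separate point; two-sided 5% is used below because it is the planned test.

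**2. Inputs the article does not give.**
- ICC: assumed 0.01, 0.05, 0.10.
- Child group size: m = 5, the middle of 4 to 6.
- Parent group size: m = 12, inferred as 24 families per cycle divided by two arms, with one parent group per cycle. This lies below the stated capacity of 15 to 20.

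**3. Type I error of the plain analysis.** Treated-arm design effect DE = 1 + (m − 1) × ICC; wait-list DE = 1. With equal arms, true SE / naive SE = √((DE + 1)/2), and true error = 2 × (1 − Φ(1.96 / SE ratio)).

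| Group size | ICC | DE | SE ratio | True error at nominal 5% |
|---|---|---|---|---|
| 5 | 0.01 | 1.04 | 1.01 | 5.2% |
| 5 | 0.05 | 1.20 | 1.05 | 6.2% |
| 5 | 0.10 | 1.40 | 1.10 | 7.4% |
| 12 | 0.01 | 1.11 | 1.03 | 5.6% |
| 12 | 0.05 | 1.55 | 1.13 | 8.3% |
| 12 | 0.10 | 2.10 | 1.25 | 11.5% |

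Simulation agrees. With 51 per arm and an unadjusted t-test (40,000 runs), child groups of about 5 gave 5.3%, 6.3% and 7.4%, and five parent groups of about 10 gave 5.6%, 7.8% and 10.4%. A simulated plain ANCOVA with 60 per arm at ICC 0.05 gave 6.1% (groups of 5) and 8.4% (groups of 12).

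**4. Power for child outcomes.** Power = Φ(0.6/√((DE + 1)/n) − 1.96), m = 5. Example at n = 45 and ICC 0.05: 0.6/√(2.20/45) = 2.714, and Φ(0.754) = 77.4%.

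| n per arm | ICC 0.01 | ICC 0.05 | ICC 0.10 |
|---|---|---|---|
| 45 (stated) | 80.5% | 77.4% | 73.8% |
| 51 (60 × 0.85) | 85.1% | 82.4% | 79.0% |
| 60 (all carried forward, d unchanged) | 90% | 88% | 85% |

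The ICC at which power falls to 80% is about 0.016 at 45 per arm and about 0.085 at 51 per arm.

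**5. Few groups.** With V₁ = DE/n, V₂ = 1/n and k treated groups, the Satterthwaite df = (V₁ + V₂)²/(V₁²/(k − 1) + V₂²/(n − 1)). Noncentral-t power for child outcomes is then about 78/74/70% at 45 per arm (nine groups) and 83/79/76% at 51 per arm (ten groups).

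**6. Parent stress, for information.** Taking the same d = 0.6 with m = 12, the normal approximation gives 84/77/68% at 51 per arm. With five parent groups and about 9 to 14 degrees of freedom, it is about 78/70/61%.

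**The case against.** **Power not delivered.** A reader might infer that the trial simply fails to reach its 80%. The article does not support that. It recruits 120 families, 14 more than the 106 calculated. At 51 per arm, child-outcome power stays at or near 80% across the assumed ICC range by normal approximation. Under intention to treat with carried-forward values, up to 60 per arm would be analysed. At the one-sided 5% that the sample size section names, 45 per arm keeps 80% up to an ICC of about 0.155 with groups of 5. What stands is narrower: at 45 per arm and the planned two-sided test there is almost no slack.

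**A shortfall against a stated power for parent stress.** This is also tempting, but the stated power concerns child attention and behavior only. The parent figures break no stated promise.

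**The inputs are assumptions.** This is true of the ICC and of the parent group size. Three centres might run more, smaller groups. The 8% to 12% errors need groups of about 12 and an ICC of at least 0.05. For child outcomes the inflation is modest. Baseline adjustment could raise power if 0.6 is on the raw standard deviation scale, which the article does not say.

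**Detail left to the analysis plan.** Random terms and degrees-of-freedom methods often are. But the article names the test, and its own sample size reproduces only under independence. That is a choice made in the text and not just a missing detail. Recruiting more families into the same groups does not remove the error inflation.

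**Conclusion.** The point holds in a conditional form. The design clusters the treated arm only, and both the stated analysis and the stated sample size ignore this. For any positive within-group ICC the plain ANCOVA gives standard errors that are too small. At ICC 0.01 to 0.10 the true two-sided error is about 5.2% to 7.4% for child outcomes and 5.6% to 11.5% for parent outcomes, the latter resting on the inferred group size of 12.

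For child outcomes the stated 80% is not assured at 45 per arm. At the planned 120 families it is broadly protected, with a small shortfall at the upper end of the ICC range or once the number of groups is allowed for. The error-rate part is firm given a positive ICC. The power part depends on an ICC and group sizes that the article does not fix.

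**What to change.** - **Data.** Record a child-group and a parent-group identifier for every treated family.
- **Analysis.** Replace the plain ANCOVA with a partially nested mixed-model ANCOVA: baseline value as covariate; a random group intercept in the FBMI arm only (child group for child outcomes, parent group for parent outcomes); wait-list families as singletons; arm-specific residual variance; Satterthwaite or Kenward-Roger degrees of freedom. Specify it before outcome data are analysed, so that it cannot look data-driven.
- **Sample size.** Keep the independent-samples figure and set beside it the power at the planned 120 families for an ICC range such as 0.01 to 0.10, with the group sizes actually expected.

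**Cost.** Revised wording, an extra identifier and some analysis work; no extra families are needed to correct the analysis. The price is wider intervals and a less favourable stated power. With only about five parent groups, the group variance for parent outcomes will be estimated imprecisely, and the report should say so.
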